## 3. Planned Intervention

The study will be developed in 5 different phases (dissemination and recruitment, pilot study, baseline data collection, implementation of the food education intervention and evaluation):

### 3.1. Phase 1: Dissemination and Recruitment

This phase corresponds to the dissemination of the project and the recruitment of participants for control and intervention groups. We organized introductory sessions with the educators and volunteers of the institutions, as well as their Pakistani users to present the project. Communication was realized in Urdu and Punjabi during the meetings with Pakistani women. Hereafter, the team of institutions and their users have helped us in the dissemination and recruitment procedure. We have also organized meetups at the different community spaces (social institutions, libraries, community centers, mosques, and female driving schools) to explain in-depth all the characteristics of the study to the interested women. In the end, we handed over to them the information sheets that sums up the principles of the study along with the informed consent. We also provided our contact and obtained the names, addresses, and contact numbers of those willing to participate in the project. We have completed this phase by forming a sample of 137 women.

### 3.2. Phase 2: Pilot Study

Six Pakistani women that will not be participate in the research will answer the Urdu version of the individual survey and they will also fill in the weekly food intake register. They will attend 3 general sessions about food education and they will be shown all the material of intervention in order to evaluate its cultural and linguistic appropriateness.

### 3.3. Phase 3: Baseline Data Collection

The data collection will be performed using a combination of quantitative and qualitative methods and techniques. From the quantitative perspective, the participants will answer an individual survey in Urdu guided by a multilingual nutritionist, that will collect the data about the sociodemographic, health and life quality, anthropometric and dietary aspects. In this same individual meetup, we will deliver a register about their weekly food intake and a guide on food portions specifically elaborated for the Pakistani population residing in Catalonia [30].

#### 3.3.1. Quantitative Variables

The outcome variables from the quantitative perspective are the following:

(a)Sociodemographic Data

Sociodemographic data that includes age, place of birth, marital status, academic studies, employment, languages, religion, the reason for migration, years of residence in Catalonia, and household members and their professions will be identified with the baseline survey

(b)Health Status and Quality of Life

The survey will include some questions regarding the health status of participants. They will also answer the SF12 questionnaire in the English version [31] which will help us to determine the health perception and the quality of life of participants.

(c)Nutritional Status

The nutritional status will be defined by anthropometric measurements (weight, height, and waist).

(d)Nutritional Knowledge and Culinary Skills

The survey will include an ad hoc questionnaire of 14 questions about nutritional knowledge (ability to distinguish different types of fats, familiarity with the main sources of macronutrients, knowledge about portion and frequency of consumption of different food groups, ability to read and interpret food labels and food beliefs) and 13 questions about skills (menu planning, preparing a grocery list, differentiating food groups, knowing about seasonal food, reading and interpreting food labels, preparing food with different culinary techniques, reusing food leftovers and preparing a healthy plate).

(e)Dietary Pattern

The dietary pattern will be studied through 3 instruments: (1) A survey, which will include questions about the number of daily meals, timing and place of meals, and company. (2) A Food Frequency Questionnaire (FFQ) inspired by the Table of Indicative Frequencies of the Spanish Society of Community Nutrition (SENC) [32]. (3) A weekly food record in which they indicate the type and quantity of food and drinks and the cooking methods with the help of a portion size guide specifically prepared for the participants [30] and specify the number, place, and time of the meals that they had in a week. This information will help us to assess the levels of energy consumption and the content of nutrients.

(f)Cultural and Linguistic Adequacy

At the end of the sessions, participants will answer an ad hoc satisfaction questionnaire about the linguistic, cultural, and content comprehension issues.

From the qualitative perspective, we will conduct 6 focus groups (3 in each municipality) to determine the cultural and religious beliefs related to food and the strengths and limitations of the current dietary pattern of the participants. The information obtained from the focus group will also serve us to adopt the intervention according to the sample’s needs. Their duration will be of 90 min.

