Due to the similarity in the sociocultural and linguistic profiles [5], mostly the research in health and nutrition is conducted jointly for all the immigrant South Asian (SA) population, especially for those who proceed from India and Pakistan. It is well established that the migrant SA population tends to have a higher risk for the development of type 2 diabetes and cardiovascular disease (CVD) compared with the western population [13,14]. In such a way that the risk of developing type 2 diabetes is two to four times higher in SA as compared to Europeans [8,15,16]. They are also affected by CVD approximately a decade earlier than the Western population [17] as 25% of myocardial infarctions occur in SA under 40 years of age and more than 50% of deaths from CVD occur in SA under 50 years of age [18]. Furthermore, they have more body fat and less lean tissue than white people of European descent at any Body Mass Index (BMI) level [16,17]. SA also tends to have lower high-density lipoprotein (HDL), higher triglycerides, and increased lipoprotein (a) as compared to other ethnicities [16,17]. The prevalence of hypertension is also slightly higher in them [13]. The reunification of these factors is established as metabolic syndrome (MetS) [19]. Currently, the prevalence of MetS in SA immigrants is estimated to be 50% in the United States and 40% in the United Kingdom [19,20].

Apart from the genetic and metabolic factors, dietary and lifestyle changes caused by acculturation, account for the high prevalence of MetS in SA immigrants [5,16,17,20]. In addition to this, cultural and linguistic barriers make it difficult for them to participate in the standard health promotion programs [5,17,21]. Consequently, their health deteriorates throughout their stay in Western countries [22,23].

Different countries have successfully designed and implemented culturally and linguistically adapted health promotion programs to address this situation. A recent meta-analysis found a 35% of reduction in diabetes in SA immigrants who participate in culturally and linguistically appropriate lifestyle modification interventions [9].

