### 2.2. Study Setting and Participants

This project is being carried out in the province of Barcelona, specifically in the region of Barcelonès, which is home to more than half of the foreign population of Pakistani origin residing in Catalonia [2]. Concretely, this study is taking place in Badalona and Santa Coloma de Gramenet which are two neighboring municipalities and, respectively, the second and fourth most populous in Catalonia by the Pakistani population [29].

Pakistani women living in these municipalities have the support of Fundació Ateneu Sant Roc (Badalona) and Casa Àsia (Santa Coloma de Gramenet), two institutions working with the same goal: the integration of migrant people into the host society and its environment. Both institutions accepted to participate and signed the consent form to participate in the research. Annually, Fundació Ateneu Sant Roc and Casa Asia attend between 50 to 60 Pakistani adult women. We have invited all of them and their close acquaintance to participate in the study. To facilitate the participation of Pakistani women in this community-based project we have set the inclusion and exclusion criteria as wide as possible (Table 1).

70 women associated with Casa Asia and 67 from Fundació Ateneu Sant Roc have accepted to become part of the study forming a sample of 137 women. There are three factors that indicate the homogeneity of the sample; firstly, the majority of the participants are in the process of learning Spanish and Catalan from the collaborating institutions, secondly, by belonging to the neighboring municipalities, their socioeconomic and sociodemographic conditions are similar and thirdly, all of them migrated between 2000 and 2022. So, to evade the contamination of information the participants from one institution will randomly become the control group and from the other, the intervention group.

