### 3.4. Phase 4: Implementation of the Food Education Intervention

In this phase, the food education intervention based on the Transtheoretical model [28] (Table 2) will be implemented. The participants from one entity will become the control group and from the other the intervention group.

The educational sessions will be done in small groups (12–15 women) to ensure the creation of positive dynamics and to create a trustworthy environment. There will be 6 subgroups of women for the intervention group and 5 subgroups for the control group. The intervention group will participate in 10 educative sessions for 10 weeks, while the control group will attend 3 sessions. Each weekly session will have a duration of 90 min.

Due to the linguistic barriers, the sessions will be carried out in Urdu and Punjabi by a plurilingual nutritionist. All the educational material will also be translated into Urdu. The learning outcomes related to educative sessions are summarized in Table 3. During the sessions, we will emphasize the following aspects:

Encourage healthy eating habits: Bearing in mind the cultural and linguistic aspects of participants healthy eating habits will be encouraged. We will combine the healthy characteristics of their traditional diet and combine them with innovative culinary techniques to facilitate the readoption. Apart from preparing the culturally and linguistically food adapted educational guides, we will also summarize and present some local guides such as “*Petits canvis per menjar millor* (small changes to eat better)” by the Public Health Agency of Catalonia [32] to enlighten the local guidance about health and nutrition.

Implement healthy eating behaviors: To implement the healthy eating behaviors the cooking skills of participants will be worked on. They will elaborate healthy snacks and healthy plates with the traditional ingredients and culinary techniques.

Adherence to the program: To actively engage the participants in the study, the sessions will be theoretical-practical. At the end of every session, there will be a final activity. We will also conduct three practical workshops about healthy snacks, food labels, and healthy plates. Throughout the sessions, we will keep providing personal counseling to those who needed.

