### 3.5. Evaluation

The protocol study will include a process and an impact evaluation that will take part at the end of health education sessions, in which we will collect the same variables that were gathered during the baseline data collection. The only modification will be the addition of an ad hoc satisfaction questionnaire to comprehend the linguistic, cultural, and content comprehension issues. We will also repeat the 6 focus groups in order to assess the changes in food and health beliefs and nutritional knowledge and skills. Photovoice technique will also help us to determine the improvement in the eating habits, and nutrition knowledge of participants. The evaluation procedure will be repeated at 3 and 6 months.

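### The protocol fixes the SF-12 in English but says the survey that collects quality of life is in Urdu; the two statements must be reconciled and one fixed version named before baseline.

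*Protocol article*

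**What the plan says.** Section 3.3.1(b), on health status and quality of life, states: "They will also answer the SF12 questionnaire in the English version". It gives the SF-12 the task of determining perceived health and quality of life. No other quality-of-life instrument is named.

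Elsewhere the article describes data collection in Urdu:

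- Section 3.3 (Phase 3, baseline): "the participants will answer an individual survey in Urdu guided by a multilingual nutritionist". The same sentence describes this as a survey "that will collect the data about the sociodemographic, health and life quality, anthropometric and dietary aspects".
- Section 3.2 (Phase 2, pilot): six women outside the trial "will answer the Urdu version of the individual survey". No English instrument is mentioned.
- Section 3.4 (Phase 4, intervention): "Due to the linguistic barriers, the sessions will be carried out in Urdu and Punjabi by a plurilingual nutritionist".

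On the women's languages, section 2.2 says that "the majority of the participants are in the process of learning Spanish and Catalan from the collaborating institutions". English is not mentioned there. Section 3.5 repeats the measurements after the sessions ("we will collect the same variables that were gathered during the baseline data collection"), and again at 3 and 6 months.

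**The concern.** The choice of English is stated outright, so it is not a detail left to a fuller document. It does not fit the rest of the plan, in which recruitment meetings, survey, pilot, sessions and teaching material all use Urdu or Punjabi.

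If the sentence is followed as written, a woman without enough English has two routes to an answer. She can respond to items that she may not understand, or she can rely on the nutritionist to interpret them aloud, and the article identifies no fixed Urdu wording for that. The first adds measurement error. The second lets the wording of an item vary between women, and for the same woman between visits. In both cases the SF-12 scores may not be comparable across women or over time, and change over time is what the evaluation is meant to assess.

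**Working it through.** The protocol article gives no figure for the SF-12: no reliability, standard deviation, target difference or power. There is nothing to reproduce, so the check sets the statements side by side.

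**1. Which language is the quality-of-life measure in?** Section 3.3.1(b) says English. Section 3.3 says that the survey covering quality of life is in Urdu. Since the SF-12 is the only named quality-of-life instrument, there are two readings:

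- *Separate form.* The SF-12 is an English form given in addition to the Urdu survey. The word for "also" in 3.3.1(b) favours this. The pilot in section 3.2, which mentions only the Urdu survey, would then not cover it.
- *Embedded items.* The SF-12 items sit inside the Urdu survey, and the mention of English names the cited source form. Sections 3.2 and 3.3 allow this. The pilot would then cover the items, but 3.3.1(b) misdescribes what the women answer, and no Urdu SF-12 is identified.

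The text needs correcting under either reading.

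**2. Is there a stated basis for using English?** No. Table 1 requires adult age, Pakistani origin, residence in one of the two municipalities and willingness to take part; it has no language criterion. Languages are among the sociodemographic items still to be collected at baseline (section 3.3.1(a)). The one language fact given for this sample, in section 2.2, concerns Spanish and Catalan.

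**3. How many administrations are exposed?** The sample is 70 + 67 = 137 women (section 2.2). The occasions are baseline, end of sessions, 3 months and 6 months, which makes 4 (sections 3.3 and 3.5). The maximum is 137 × 4 = 548 administrations if every woman completes every visit. This counts forms affected by the ambiguity; it does not measure error.

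**4. Can the error be sized?** No. That would need the reliability of the SF-12 in these women under each form of administration, or at least the share with adequate English. The article gives neither.

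**The case against.** The strongest reply is that the embedded reading is the natural one. The Abstract and section 3.3 both place quality of life within the survey that the nutritionist helps the women complete, and section 3.3 says that this survey is in Urdu. On that reading the only fault is a loosely worded reference to the source form. This stands as a possibility, and it is why the point is framed as a contradiction to be reconciled rather than as proof that English will be used.

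Second, a multilingual nutritionist guides every survey, which makes plain non-comprehension less likely. This also stands, but help with understanding does not fix the wording of the items.

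Third, interviewer scripts usually belong in the full protocol, so their absence from an article is no defect. Agreed. The point rests on the language that the article does state.

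A reader might go further and draw three stronger conclusions that the document does not support:

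- *That the SF-12 results will be invalid.* English proficiency is not reported. The general remark in the Introduction that "cultural and linguistic barriers make it difficult for them to participate in the standard health promotion programs" does not establish that these women cannot read English. Language is also only one of several reasons given for the programme.
- *That oral translation will differ by arm.* Allocation is by institution, so an interviewer might know the arm. However, the article does not say that the person collecting data also leads the sessions, and it describes no mechanism by which translation would differ by arm. Knowledge of the arm would in any case affect every interviewer-guided outcome, whatever the language of the SF-12.
- *That a definite loss of precision or effective sample size follows.* Any such figure would rest on reliabilities invented for the purpose.

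**Conclusion.** The contradiction is real. Section 3.3.1(b) puts the SF-12 in English, while sections 3.2 and 3.3 put the survey that collects quality of life in Urdu. If English is used as written, the scores risk comprehension error or unstandardised oral interpretation, and so risk not being comparable between women and visits. That risk depends on some women lacking adequate English. Nothing in the article excludes this, since English is not an entry requirement, but nothing states it either.

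The weight is moderate. Up to 548 administrations of the only named quality-of-life instrument are involved, and baseline answers taken in an unsuitable form could not be recovered later. Against that, the SF-12 is one of several outcomes and is not named as primary. A problem with it would leave the diet, knowledge, skills and anthropometric results intact.

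**What to change.** Reconcile sections 3.3 and 3.3.1(b) before baseline:

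1. In 3.3.1(b), replace the reference to English with one fixed written Urdu SF-12. Use a validated version if one is available, which the article does not say. Otherwise use a forward- and back-translated one and report it as such.
2. State in section 3.2 that this version is part of the Urdu survey piloted with the six women.
3. State in section 3.5 that the same wording is used in both arms at baseline, end of sessions, 3 months and 6 months.

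If the SF-12 items are already inside the Urdu survey, the change is to say so and identify the version. If they are not, the cost is a replacement form and, where no validated version can be had, a short translation step. An in-house translation would standardise the wording but would not make the instrument validated, so that limitation would have to be reported. The added burden is small because the survey is already planned, and to be piloted, in Urdu. Pilot and baseline are both described as still to come.

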#### 3.3.2. Qualitative Variables

The outcome variables from the qualitative perspective are the following:

(a)Strengths and Weaknesses of the Dietary Pattern

Through the focus groups, the participants’ traditional and current dietary patterns will be discussed. They will also describe the factors that facilitate or hinder them from following a healthy diet.

(b)Food Beliefs

The focus groups will determine the beliefs related to the consumption of different foods, their effects on health and well-being, the opinion on herbal products, the myths related to food and health, etc.

(c)Nutrition and Health Knowledge

The focus group will also help us to figure out the health and nutrition literacy of participants to adopt the intervention on their requirements.

### 3.4. Phase 4: Implementation of the Food Education Intervention

In this phase, the food education intervention based on the Transtheoretical model [28] (Table 2) will be implemented. The participants from one entity will become the control group and from the other the intervention group.

The educational sessions will be done in small groups (12–15 women) to ensure the creation of positive dynamics and to create a trustworthy environment. There will be 6 subgroups of women for the intervention group and 5 subgroups for the control group. The intervention group will participate in 10 educative sessions for 10 weeks, while the control group will attend 3 sessions. Each weekly session will have a duration of 90 min.

Due to the linguistic barriers, the sessions will be carried out in Urdu and Punjabi by a plurilingual nutritionist. All the educational material will also be translated into Urdu. The learning outcomes related to educative sessions are summarized in Table 3. During the sessions, we will emphasize the following aspects:

Encourage healthy eating habits: Bearing in mind the cultural and linguistic aspects of participants healthy eating habits will be encouraged. We will combine the healthy characteristics of their traditional diet and combine them with innovative culinary techniques to facilitate the readoption. Apart from preparing the culturally and linguistically food adapted educational guides, we will also summarize and present some local guides such as “*Petits canvis per menjar millor* (small changes to eat better)” by the Public Health Agency of Catalonia [32] to enlighten the local guidance about health and nutrition.

Implement healthy eating behaviors: To implement the healthy eating behaviors the cooking skills of participants will be worked on. They will elaborate healthy snacks and healthy plates with the traditional ingredients and culinary techniques.

Adherence to the program: To actively engage the participants in the study, the sessions will be theoretical-practical. At the end of every session, there will be a final activity. We will also conduct three practical workshops about healthy snacks, food labels, and healthy plates. Throughout the sessions, we will keep providing personal counseling to those who needed.

Empowerment: The implementation of the sessions in small groups will promote socialization and sorority among participants. We will highlight the impact of the eating habits of Pakistani women on their families and we will invite them to extend the role of healthy eating habits to the rest of the community.

### 3.5. Evaluation

The protocol study will include a process and an impact evaluation that will take part at the end of health education sessions, in which we will collect the same variables that were gathered during the baseline data collection. The only modification will be the addition of an ad hoc satisfaction questionnaire to comprehend the linguistic, cultural, and content comprehension issues. We will also repeat the 6 focus groups in order to assess the changes in food and health beliefs and nutritional knowledge and skills. Photovoice technique will also help us to determine the improvement in the eating habits, and nutrition knowledge of participants. The evaluation procedure will be repeated at 3 and 6 months.

